## Abstract

**Background:**

Recent advances in Computational Intelligence Tools and the escalating need for decision-making in the face of complex and uncertain phenomena like pandemics, climate change, and geopolitics necessitate understanding the interaction between these tools and human behavior. It is crucial to efficiently utilize the decision-makers cognitive resources in addressing specific problems.

**Methods:**

The main goal of this present protocol is to describe the effect that CITs (Computational Intelligence Tools) have on decisions made during complex and uncertain situations. It is an exploratory study with a mixed methodology. Solomon’s group experiment design includes a narrative analysis of cognitive features such as integrative complexity (IC), cognitive flexibility (CF), and fluid intelligence (FI). Additionally, measures of neural activity (NA), physiological measures (PM), and eye-tracking data (ET) will be collected during the experimental session to examine the marginal impact of these processes on decision outcomes (DO) and their relation to CIT capabilities. To achieve this objective, 120 undergraduate and graduate students involved in decision-making will participate as subjects. The approximate duration of the study will be 2 years. Strict adherence to the relevant ethical considerations will be maintained during the performance of the experimental tasks.

**Discussion:**

The study will provide valuable information on CITs’ effect on decision-making under complex and uncertain contexts. This will help to better understand the link between technology and human behavior, which has important implications. CIT designers can use future results and at the same time, it will be possible to understand cognitive, behavioral, physiological processes, and even the subjective assessment of individuals when they use technological tools to solve a problem.

## Introduction

Despite considerable advances in the application of computational intelligence tools in decision-making processes, decision-makers struggle to keep up with complex and uncertain phenomena such as pandemics, climate change, and geopolitics. In recent years, the sharp rise in the availability of modern computational intelligence tools, such as automated data collection methods, satellite image processing, machine learning, artificial intelligence, and highly disaggregated simulation models, has attracted the attention of decision scientists. These tools present a potential opportunity to generate, collect, and analyze new data to enhance decision-makers’ abilities to respond to rapidly evolving decision environments.

From this perspective, computational intelligence tools (CITs) could be used as cognitive prostheses that expand the cognitive bandwidth of decision-makers, enabling them to more efficiently utilize their cognitive resources to address uncertainty and complexity in decision situations [1,2]. The concept of cognitive bandwidth, proposed by Mullainathan and Shafir [3], explores information saturation that decreases a person’s cognitive abilities and executive control. The authors provide empirical evidence of this concept through decreased performance in decision-making processes, psychometric tests, and even behavior patterns, such as the inability to follow a diet or adhere to treatment.

Recent progress in cognitive science and computational intelligence offers an opportunity to develop an integrated theoretical framework to study the interaction of CITs with human decision-makers in high-stakes decision contexts. For example, CITs can improve the decision-making process in crises providing decision-makers with new data, enabling quick estimation of likely consequences in a broader range of circumstances, and facilitating the identification of key decision trade-offs [4]. However, if CITs are implemented in a way that overwhelms users with excessive detail and complexity. In that case, it can lead to cognitive overload, confusion, mistrust, or deadlock, particularly in circumstances that require rapid action.

This interdisciplinary approach can contribute to: 1) objectively illustrating the belief and value models of decision-makers, 2) identifying the impact and mechanisms through which CITs influence individuals’ integrative complexity traits, 3) supporting CIT interventions in crises, and 4) contributing to the development of current decision sciences. Ultimately, this integrative approach may result in formal cognitive decision-making models under uncertainty and complexity, providing the scientific community with a deeper understanding of the mechanisms by which CITs and decision-makers interact in rapidly evolving learning environments.

## Method

### Research question

What is the marginal impact (i.e., the difference between performance in the and control condition) of the components of the TICs on people’s cognition and performance in complex and uncertain decision-making environments?

### Main objective

Describe the effect of CITs on decisions made during complex and uncertain situations.

#### Secondary objectives

Determine the relationship of the experimental parameters of the TICs with a positive impact of decision-makers’ ability to deal with a complex and uncertain environment.

Determine the combination of experimental parameters of the TICs that positively impact the level of integrative complexity of individuals when faced with an ambiguous, or deeply uncertain problem.

Determine the combination of experimental parameters of CITs that lead to mistrust, excessive technological dependence, model rejection or stagnation in complex and uncertain environments.

Evaluate the marginal impact of CIT components on people’s cognitive bandwidth in complex and uncertain decision-making environments.

Evaluate the CIT components’ marginal impact on the integrative complexity of people in complex and uncertain decision-making environments.

### Hypothesis

#### Null hypothesis

There is no effect of the CITs on the decisions that are made in complex and uncertain scenarios.

#### Alternate hypothesis

There is an effect of the CITs on the decisions made in complex and uncertain scenarios.

## Study design

### Study description

This phase 0 randomized controlled study that utilizes the Solomon cluster experimental design to assess the relationship between using CITs and decisions made during complex and uncertain situations. Potential populations for this study include undergraduate and graduate students, and decision-makers, given their close involvement in day-to-day decision-making processes. Participants will engage in decision-making strategies using a standardized interface, focusing on a classic decision-making problem known as Ellsberg’s paradox. No incentives or monetary resources will be at stake during the study. The participants’ psychophysiological responses will be recorded: blood pressure volume, respiration rate, skin conductance level, and EEG activity. Additionally, participants will complete standardized pencil-and-paper intelligence tests.

### Fundamentals of study design

CITs and ambiguity are defined and controlled variables.

### Fundamentals for the population of research subjects

Educational and professional settings are full of decisions that can be tied directly to an outcome. Undergraduate, graduate, and professional students are usually people of legal age who express their authorization for the study. In addition, this population may reveal valuable decision-making insights from their settings that increase the study’s external validity.

### Rationale for stratification factors

The participants in this study will consist of undergraduate or graduate students, and professionals from Tecnológico de Monterrey. All participants will be recruited through their teachers using a script and subsequently contacted via email to schedule an appointment in the study environment. The study topics will not be disclosed in class, and there will be no rewards or penalties for participation. All participants must volunteer and provide informed consent approved by the ethics committee of Tecnológico de Monterrey in Mexico.

One hundred and twenty (undergraduate and graduate students) will be divided into four research groups (RG). Each RG will comprise 30 individuals, with equal representation of 15 men and 15 women from various disciplinary backgrounds. The assignment of participants to each research group will adhere to the following experimental criteria:

RG 1: No computational system or ambiguity

RG 2: Unambiguous computer system

RG 3: Computational system with ambiguity

RG 4: Ambiguity without a computer system

Participants in the research groups will be carried out randomly while considering factors such as age, educational level, and sex to reduce intergroup variability. Each subject will belong to only one group and will participate in a single experimental session to avoid maturation and memory effects.

Regarding cognitive abilities, these factors will be analyzed post hoc to identify cognitive patterns associated with using CITs within the studied sample. Stratification based on cognitive conditions will not be conducted a priori, as the literature reports contradictory results between these conditions and the use of CITs and integrative complexity [8,9].

### Recruitment and inclusion/exclusion/suspension criteria

Following a maximum variation sampling logic; (maximum variation sampling involves selecting a diverse range of variations on the dimension of interest to accurately document unique or varied variations that identify common patterns throughout the sample [10]. This type of sampling is ideal for the present research, considering the theoretical gaps observed in the literature regarding the relationship between cognitive variables and the use of decision support tools.

The participants will be 120 subjects (undergraduate, graduate, and professional students) will be divided into four research groups (RG). Each RG will be composed of 30 individuals (15 men and 15 women with diverse disciplinary backgrounds) according to Solomon’s group experimental design. All participants will be recruited voluntarily and give their informed consent for the study, approved by the Ethics Committee of the Tecnológico de Monterrey in Mexico. The study only contemplates healthy subjects, so the term patient will be changed to that of participants.

### Inclusion criteria

The inclusion criteria for this study are intentionally general, given the exploratory nature of the research. The aim is to investigate the use of CITs without imposing many predefined criteria. Only exclusion criteria reported in the relevant literature, which are most closely related to potential variability in the data, will be considered.

Participants over 18 years of age.

Being an undergraduate or postgraduate student or exercising a professional activity.

Their professional or academic environment will not be directly associated with the specific context of the research for decision-making.

Participants who signed the informed consent

### Exclusion criteria

All eligibility and exclusion criteria will be inquired when confirming the appointment, and candidates will be assessed based on self-reporting to determine their suitability to participate in the experimental session. If a suppose a candidate does not meet the eligibility criteria. In that case, an explanation&explanation will be provided, and they will be invited to remain interested in the study’s results and maintain communication with the research team. The emphasis is on ensuring that individuals do not feel excluded for social reasons but rather for technical reasons related to the study.

Being left-handed.

This feature is an exclusion criterion because the literature on the use of EEG reports that the left hemisphere may favor some skills, i.e. the language skills of right-handed people may be 20% higher than left-handed people [11].

History of drug abuse.

Substance abuse has been associated with neurological disorders associated with atypical measures in the use of electroencephalographic recording measures, including cocaine, opiates, ecstasy, and cannabis [12]. For these reasons, the subjects will be asked if they have a history of illegal substance abuse and if their answer is affirmative, the subjects will be excluded from their participation.

Conditions of vulnerability.

All research involves risks, and defining vulnerability is complex and challenging. Consequently, in the present study, any participant will be excluded if their social conditions, which include experiencing different forms of poverty or facing displacement difficulties, could be negatively impacted by participating in an unpaid activity for an extended period. Additionally, pre-existing health conditions, such as a history of mental health illness, pregnancy, or any reported illness by the subject, will serve as exclusion criteria due to the increased risk associated with interventions for these individuals.

Be a student of one of the researchers.

To prevent reactance, social influence, or submission phenomena, individuals involved in a teacher-student relationship with research team members will be excluded from this study due to concerns regarding potential issues of subordination.

History of epileptic or convulsive episodes.

Although the case is rare, the use of EEG is contraindicated in patients with a history of epilepsy or seizures unless it is performed for diagnostic purposes.

### Suspension criteria

Discomfort during the session.

This criterion refers to any sensations of discomfort, pain, or displeasure reported by the research subject. It will be specified before initiating any registration or placement of equipment on the participant, and emphasis will be placed on notifying the research team at any time during the session if such sensations arise. In such a situation, the study will be suspended, and any potential human error in equipment placement or stimulus presentation will be reviewed. The participant will be informed of the situation and given the option to restart the session. If the participant chooses not to continue, the session will be concluded, and they will be allowed to leave the premises when they feel ready to do so.

Presence of auras.

According to Fernández Torre [13], "The epileptic aura is the part of a seizure that occurs before the loss of consciousness and is remembered. The surface electroencephalogram often fails to detect changes during an isolated aura. A feeling of fear is the most common affective symptom associated with epileptic discharges of mesial temporal origin. Somatosensory auras may include numbness, tingling, electrical sensations, or occasionally pain."

For the reasons above the participants will be informed to be aware of the presence of perceptible sensations of unidentified origin, as described by Fernández. If any of these sensations occur, the study will be immediately terminated, and the participant will be kept under observation by the research team for at least 60 minutes before leaving the facility.

Reporting of stress or headache.

Any feelings of stress, such as frustration, intense anger, or sweating, or a headache, will warrant suspending the study. The participant will remain at rest until they state that they feel calm and ready to leave the facilities.

### Study evaluations

Informed consent forms and selection record.

The informed consent form will be provided to the participant at the beginning of the first session. It will be emphasized that they have ample time to read it carefully. Once the participant indicates that they have finished reading, any questions or doubts will be addressed. A brief explanation of the study, its objectives, and research questions will be provided. Only when the participant fully approves and understands the procedures will their signature be requested.

All collected informed consent forms will be securely stored in a locked cabinet in the investigator’s office. The research team will maintain a participation record to document the details of each selected participant and to confirm their eligibility or rejection based on the exclusion criteria.

### Research methodology

The research team will design a decision-making stimulus situation based on standardized decision-making paradigms validated in the existing literature, such as Ellsberg’s paradox. The characteristics of this decision-making situation will include non-linear behavior, multi-criteria results, ambiguity, and uncertainty. The stimulus parameters and narrative will be designed through computational experimentation to identify viable and robust interventions to serve as a baseline for analysis.

The stimulus situation will always be defined by choice interfaces that do not threaten the participants and will not involve monetary resources or real economic gains. These interfaces will be developed based on previously standardized situations described in the available literature, with defined parameters of ambiguity and validated performance in computational interfaces, such as Ellsberg’s paradox.

The Ellsberg paradox is an experimental challenge where participants make decisions about a possible outcome based on the probability of an event occurring [14]. This paradox is frequently used in decision-making theory [15,16]and has modulations in terms of ambiguity (amount of information offered to the decision-maker) and uncertainty (random result).

The experimental task of the Ellsberg paradox involves making a series of bets (without involving economic resources, only predictions) on the random selection of a colored ball in a lottery. The balls are red, green, or blue, and participants receive information about the total number of balls in a container, which varies in each round. Three decision conditions are presented to the participants. In the first condition, complete information is provided for each betting option, allowing participants to estimate which ball is most likely to be chosen. In the second condition, ambiguity is introduced by combining the frequency information of two balls into a single category, making it impossible for participants to determine which ball is more frequent and thus has a higher probability of being chosen in the lottery. In the third condition, participants are provided with a decision support tool that presents information about the probability of selecting each ball, considering all possible container frequency combinations (see Appendix 1 for images of the interface).

The CIT will be an expert system based on artificial intelligence (SSEE), utilizing previous knowledge from the literature and the response options of the stimulus situation. Artificial intelligence will simulate the knowledge of an expert to solve a specific problem effectively. The resulting CIT will be unanimously validated by three expert judges in the use of computational tools in decision-making.

Participants will be presented with the interface, and only two research groups (RGs) will be asked to use the CIT to study the situation. Participants will have time to explore the decision-making situation and be guided through various phases of the interface. The decisions made by the participants will be entered into the CIT, which will provide feedback on the results of their decisions.

The experimental procedures will be divided into three steps, following the Solomon group experimental design. According to McCambridge et al. [17], Solomon’s 4-group design involves randomly assigning participants to four possibilities: (a) an experimental group with evaluations, (b) an experimental group without evaluations, (c) a control group with no assessments, and (d) a control group with no assessments. This design enhances internal validity by controlling for the effects of the baseline estimate and the interactions between the intervention and the baseline assessments.

Given that the present study examines the use of CITs in situations of ambiguity, the Solomon group design is an appropriate measure to observe the interaction between these variables within a single experimental design. The following groups will be established for the sample:

RG 1: No computational system or ambiguity

RG 2: Unambiguous computer system

RG 3: Computer system with ambiguity

RG 4: Ambiguity without the computer system

The inclusion of participants in the research groups will be carried out randomly, considering stratification and pairing factors based on their age, educational level, and sex to reduce intergroup variability. Each participant will belong to only one group and will participate in a single experimental session to avoid maturation and memory effects.

Regarding cognitive abilities, these factors will be analyzed post hoc to identify cognitive patterns associated with the use of CITs within the studied sample. Stratification based on cognitive conditions will not be conducted a priori, as the literature reports contradictory results regarding the relationship between cognitive abilities, using the CITs, and integrative complexity [8,9].

The procedure consists of the following steps:

STEP 1: Each participant will be scheduled for a visit to the decision theater of the Tecnológico de Monterrey, where they will be assigned to an experimental group and participate in a session on the stimuli used in the experiments. All groups will participate in an orientation session. Two groups will use the CIT during the stimulus, while the others will not have access to it. Eye tracking, physical activity, and EEG waveband activity data will be recorded in real-time throughout the session.

STEP 2: The social and cognitive characteristics of the participants will be assessed through surveys and standardized tests during a second visit to the decision theater of the Tecnológico de Monterrey. Participants will complete two psychometric tests measuring Verbal Intelligence (Terman-Merrill) and non-verbal intelligence (Beta 4).

STEP 3: All groups will be scheduled for a follow-up session in the laboratory. During this session, participants will receive feedback on the study’s results, discuss their experience solving the stimulus, and reflect on the using of CITs. The final results will also be shared with the participants. If participants cannot attend this step, an individual dossier containing their results and variable information will be sent to them.

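### The trial is called a Solomon design and credited with control of baseline-assessment effects, but its four groups form a 2×2 factorial (CIT by ambiguity) that cannot provide that control

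*Protocol article*

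**What the plan says.** The Solomon label appears in the Abstract (Methods), in Recruitment and inclusion/exclusion/suspension criteria, in Research methodology, and in Study description, which opens: "This phase 0 randomized controlled study that utilizes the Solomon cluster experimental design".

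Research methodology describes a Solomon design as four randomised arms that differ by intervention and by assessment, and says: "This design enhances internal validity by controlling for the effects of the baseline estimate and the interactions between the intervention and the baseline assessments". The last two arms in that description read "c) a control group with no assessments, and (d) a control group with no assessments", so they are identical and the pretested control arm is lost.

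The next paragraph adopts the design for this trial, on the ground that "the Solomon group design is an appropriate measure to observe the interaction between these variables within a single experimental design". The variables meant are use of the CIT and ambiguity.

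The groups are then listed: "RG 1: No computational system or ambiguity", "RG 2: Unambiguous computer system", "RG 3: Computer system with ambiguity", and RG 4, which the list in Rationale for stratification factors gives as "RG 4: Ambiguity without a computer system". The two lists agree. Each participant is randomised to one group, with account taken of age, educational level and sex, and attends one experimental session.

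**The concern.** A Solomon design crosses treatment with the presence or absence of a pretest. Comparing pretested with unpretested groups is what separates the effect of being pretested, and its interaction with treatment, from the treatment effect. In this trial the second factor is ambiguity. The protocol thus claims a protection of internal validity that its groups do not supply, and a results paper that repeats the claim would mislead readers about the core design.

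The label also draws attention away from what the four cells can answer, namely whether the effect of the CIT differs with and without ambiguity. The protocol gives that interaction as its reason for the design, yet the one model it states has no ambiguity term. Design name and model both miss the second manipulated factor.

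The word *cluster* in Study description adds to the confusion, because no clusters are randomised.

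**Working it through.** **Inputs**
- Group definitions: Rationale for stratification factors and Research methodology.
- Size: 30 per group, 120 in total (Rationale for stratification factors).
- Timing: signals are recorded during the experimental session (Step 1), and psychometric tests are given at a second visit (Step 2). No measurement of decision outcome or integrative complexity before the intervention is described.
- Stated model: Methods and models of data analysis according to the type of variables.

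**1. The plan's own figure.** 4 × 30 = 120, which reproduces. No alpha, power, effect size or SD is given, so there is no sample-size calculation to check.

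**2. Coding of the groups**

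| Group | CIT | Ambiguity | Pretest |
|---|---|---|---|
| RG 1 | 0 | 0 | same value *p* in all groups |
| RG 2 | 1 | 0 | *p* |
| RG 3 | 1 | 1 | *p* |
| RG 4 | 0 | 1 | *p* |

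**3. What can be estimated**
- Intercept, CIT, ambiguity, CIT × ambiguity: rank 4 of 4. All are estimable.
- The same, plus pretest and CIT × pretest: rank 4 of 6. With *p* = 0 both added columns are zero. With *p* = 1 the pretest column equals the intercept and the CIT × pretest column equals the CIT column. Neither added effect is estimable in either case.
- A true Solomon layout, with rows (treatment, pretest) = (1,1), (1,0), (0,1), (0,0) and terms for intercept, treatment, pretest and their product: rank 4 of 4. Both pretest effects are estimable.

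**4. What a pretest factor would take.** Crossing CIT, ambiguity and pretest gives 2 × 2 × 2 = 8 cells, or 120 / 8 = 15 per cell. The plan has four cells of 30.

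**5. Precision of the factorial contrasts.** The documents give no SD, so I assume SD = 1 and report standard errors in SD units:
- CIT or ambiguity main effect, 60 v 60: √(1/60 + 1/60) = 0.183
- CIT effect under ambiguity, RG 3 v RG 4: √(1/30 + 1/30) = 0.258
- CIT × ambiguity, as a difference of differences: √(4/30) = 0.365

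These do not depend on what the design is called. They show that the interaction, the stated reason for the design, is estimated with twice the standard error of a main effect.

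**6. The stated model.** Its named inputs are eye tracking, neural activity, executive control, fluid intelligence and CIT version. Research groups enter through a summation index, but ambiguity is not a named input, and neither is its interaction with the CIT.

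**The case against.** The sentence on baseline effects is a general account of Solomon designs that follows a citation. The trial then adopts the design for the CIT–ambiguity interaction and does not separately assert control of a pretest effect. With no pretest described, there is no pretest sensitisation to control, so the wording biases no estimate. The duplicated arms look like a slip in a paraphrase, and *cluster* appears only once. The rank result follows directly from a constant pretest, so it formalises the mismatch and is not independent evidence of it. The study is declared exploratory, and formal contrasts are commonly left to a fuller document.

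Most of this stands as a limit on consequences, but it does not rescue the label. The procedures are said to follow the Solomon design, its benefit is stated, and the design is adopted in the next paragraph. A reader will take the benefit as claimed for this trial. No fuller document could turn these four groups into a Solomon design.

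Three stronger readings are tempting, and the protocol does not support them:
- A reader might infer that a pretest-by-treatment analysis will be run and an ambiguity effect reported as sensitisation. No such analysis is planned, and the stated model has no pretest term.
- A reader might infer that the Step 1 orientation could serve as a physiological baseline. Step 1 does not say that orientation is a recorded measurement before CIT use, and it mentions group assignment before orientation.
- A reader might call the design post-test only. That is an inference from the steps and is not stated. The conclusion does not need it, because a pretest given to all four groups would not help.

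**Conclusion.** The point holds as a misdescription of the design. The claimed control of baseline-assessment effects and of their interaction with the intervention is not a property of this trial, because no group differs by pretest. This rests only on the group definitions, which the protocol gives twice and consistently.

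The size is bounded. The randomised CIT, ambiguity and interaction comparisons remain valid, and allocation, measurements and the total of 120 are unaffected. What is lost is one claim of internal validity. What needs repair is the name of the design and the absence of ambiguity from the stated model.

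One matter must be settled alongside. Research methodology says that three decision conditions (full information, ambiguity, decision support tool) are put to participants, which fits poorly with four groups to which each person belongs only once.

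**What to change.** 1. In the Abstract (Methods), Study description, Recruitment and inclusion/exclusion/suspension criteria, and Research methodology, replace *Solomon* and *Solomon cluster* with: individually randomised 2×2 factorial (CIT yes/no by ambiguity yes/no).
2. Delete the sentence on control of baseline effects, or state that it does not apply to this trial. The faulty four-arm description can go with it.
3. State that the four cells will be analysed for the CIT effect, the ambiguity effect and their interaction, and add ambiguity to the stated model.
4. Reconcile the three decision conditions with the four groups, so that the new label describes what each participant actually receives.
5. Do not add a baseline covariate from the orientation period unless a recording before CIT use is confirmed.

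The cost is wording and the addition of ambiguity to the model. The pretest-control claim is given up. The sample size of 120, recruitment and procedures stay as they are.
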